**Fig. 1 Fig1:**
[figure not shown]
Trial schema

### Blinding

The nature of the intervention does not permit blinding of either patient or clinician, but the data entry and statistical analysis are blinded procedures. This is achieved by data entry from an electronic database using study number only, rather than identifiable patient details. Additionally, the statistical analysis is carried out on a finalised database remote from the study centre and using study numbers only.

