#### Smoking cessation program structure

A smoking cessation practitioner assesses the patient as part of the primary care giving team and measures exhaled CO. The Health Service Executive (HSE) Tobacco Cessation Support Program is a structured behavioural support program used by smoking cessation specialists in Ireland. It uses behavioural change techniques to support the tobacco user through the process of quitting by increasing confidence and motivation to quit and developing personal coping skills to sustain the quit attempt over time. Once the smoking cessation intervention is performed, a ‘quit date’ is set. The smoking cessation practitioner then sees the patient according to the following schedule:
One week post quit dateFour weeks post quit dateThree months post quit dateSix months post quit date/end of pregnancy (depending on gestation).

If a patient is still smoking at 4 weeks post quit date, NRT is offered in accordance with HSE guidelines which recommend its use in pregnancy only after a psychological intervention has failed.

The smoking cessation practitioner return visits are held in the clinic alongside the antenatal team. Current smoking status is recorded at each visit to the smoking cessation practitioner. If the patient has quit smoking, the timing of cessation and any aids used are recorded. Measures of urge to smoke, tobacco withdrawal score, and confidence in quitting are recorded. Quantitative measurement of urine cotinine is performed at 32 and 36 weeks, coinciding with the third trimester ultrasound scans. The HSE-adapted Russell Standard definitions of Quit are used [16]:
*Self-reported Quit*. This is defined as a self-report of smoking not more than five cigarettes from the quit date. A standard abstinence question is ‘Have you smoked at all since (date of start of abstinence period) A: No, not a puff; B: 1–5 cigarettes; C: More than 5 cigarettes?’ Answer A or B can be classified as a Self-reported Quit.*Validated Quit*. A Self-reported Quit that is validated with a CO monitor reading of less than 10 ppm is classified as a Validated Quit.

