### Controls

The control group is 226 patients booked and recruited at the same time and randomised to ‘routine care.’ These patients have smoking cessation advice given as a ‘once-off’ at the booking visit via verbal or written information on the HSE Quit service, which is the current routine care in the Coombe and all obstetric units in Ireland [17]. The patients will attend either a general obstetric clinic or midwifery-led clinic and have a booking scan and 20–22-week anomaly scan as normal. The control group will be divided into two groups: 113 will have an additional scan at 32 and 36 weeks to screen for intrauterine growth restriction (IUGR), and 113 will receive no additional scans unless clinically indicated by their team. This is done to ensure testing of the hypothesis that the clinic as the intervention is responsible for any difference in outcomes, rather than the provision of additional ultrasound scans.

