### Data management

Data collected in the study will be irrevocably anonymised, with patient names, hospital numbers, and routine testing specimen numbers de-identified and replaced with study numbers for the purpose of this research. The collected data will be stored in a password-protected spreadsheet on an encrypted computer and will be exported as a dataset for statistical analysis.

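### The blinding claimed for data entry and analysis rests on study numbers and remote analysis, which conceal the woman's identity but not her allocated arm

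*Protocol article*

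**What the plan says.** The Blinding section of the protocol article accepts that neither patients nor clinicians can be blinded, "but the data entry and statistical analysis are blinded procedures". It then names the means. For data entry: "This is achieved by data entry from an electronic database using study number only, rather than identifiable patient details". For the analysis: "the statistical analysis is carried out on a finalised database remote from the study centre and using study numbers only".

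The Data management section uses the same device for a different purpose, anonymisation: "patient names, hospital numbers, and routine testing specimen numbers de-identified and replaced with study numbers".

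The arms generate different data. Under Smoking cessation program structure, women in the STOP clinic see a practitioner at set times after a quit date, and "Current smoking status is recorded at each visit to the smoking cessation practitioner". Under Controls, by contrast, "These patients have smoking cessation advice given as a ‘once-off’ at the booking visit". The controls are then split: "113 will have an additional scan at 32 and 36 weeks to screen for intrauterine growth restriction (IUGR), and 113 will receive no additional scans". Women in the second half can still be scanned where their team sees a clinical reason.

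The Statistical analysis section plans a chi-square test of STOP against all controls, a comparison of the two control groups, a comparison of growth restriction between STOP and the scanned controls, an adjustment for the stratification factors, an assessment of adherence, and a per-protocol repeat of the group comparisons.

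**The concern.** Blinding in a trial means concealment of allocation. A study number conceals identity, and someone who has only a study number can still know the arm. The article offers de-identification as if it were blinding.

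Patients and clinicians are unblinded and the primary outcome starts from self-report, so masking after data collection is the only masking this trial claims. Some judgement can remain at that stage: whether abstinence ran continuously from the quit date, whether a carbon monoxide or cotinine result validates it, and who belongs in the per-protocol population. If the final report repeats the claim, readers will credit those steps with a protection that the described procedure does not give.

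**Working it through.** No figure in the plan bears on this point, so the check is a comparison of the stated mechanism with the data and the analyses.

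**1. What each stated measure hides**

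| Measure (Blinding section) | Hides identity? | Hides arm? |
|---|---|---|
| Data entry by study number | Yes | No |
| Analysis by study number | Yes | No |
| Finalised database | No; prevents later edits | No |
| Analysis remote from the centre | Adds distance from the clinic | No |

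The article mentions no coded arm label, masked allocation variable or withheld field.

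**2. What the records show, as the article describes them**

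| Data | STOP | Scanned controls (113) | Other controls (113) |
|---|---|---|---|
| Practitioner visits at 1 week, 4 weeks and 3 months after the quit date, and at 6 months or end of pregnancy | Yes | Not described; one-off advice at booking | Not described; one-off advice at booking |
| Urge, withdrawal and confidence recorded at practitioner visits | Yes | Not described | Not described |
| Study scans at 32 and 36 weeks | Yes | Yes | Only if clinically indicated |

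A record with practitioner follow-up points to STOP. A record with third-trimester scans but no practitioner follow-up suggests a scanned control. A record with neither suggests an unscanned control. The inference is imperfect. Scan fields alone do not separate STOP from scanned controls, some unscanned controls will have clinically indicated scans, and a STOP woman who misses her visits may have empty practitioner fields. The supportable statement is that many records reveal the arm.

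**3. What the planned analyses require**

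- Primary chi-square test, STOP against all controls: two groups of about 225 and 226 (113 + 113). This can be run under a neutral two-level code, and the group sizes give nothing away.
- Comparison of the two control groups, and of STOP with the scanned controls: both need the three-group code.
- Adherence and per-protocol analyses: both need to know what each woman received, and so her arm.

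Only the primary test, with its adjustment for the stratification factors, can realistically be run without sight of the arm.

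**4. How sensitive the primary result is to reclassification**

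Inputs: 9% and 18% cessation (Sample size justification), 225 STOP women (same section) and 226 controls (Controls).

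- Expected quitters: 225 × 0.18 = 40.5 and 226 × 0.09 = 20.3, taken as 40 and 20.
- Chi-square test without continuity correction, 40/225 v 20/226: p = 0.005.
- Four STOP quitters reclassified as smokers, 36/225 v 20/226: p = 0.021.
- Seven reclassified, 33/225 v 20/226: p = 0.055.

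At the planned rates, about seven women would have to be reclassified, all in one direction, before significance at 5% was lost. These counts illustrate sensitivity; nothing in the article suggests that such errors will occur.

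**The case against.** The strongest reply is that the Blinding section is a few sentences in a condensed article. Coded arm labels, withheld fields and the time of unmasking usually sit in the full protocol or the analysis plan, which are not shown. That is fair as far as it goes, and for that reason a reader should not infer that no blind exists anywhere in the trial. An unseen document may mask the arm for the primary test. The point stands because the article does more than leave the mechanism out: it names one, and that one does not conceal allocation. No label-masking for the statistician would make the data-entry claim true either.

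Three other stronger readings are tempting and should be resisted.

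- *The arm can be read for practically every woman.* The database layout, the assessment schedule figure and the additional file are not shown, and the overlaps listed in the working leave some records ambiguous.
- *The group sizes unmask the analysis.* Sizes of about 225, 113 and 113 matter only in three-group tables. They reveal nothing in the primary comparison of about 225 with 226.
- *A handful of reclassified women would overturn the result.* Four would not at the planned rates. The outcome is also tied to the Russell Standard, with a fixed three-option question and a carbon monoxide cut-off of 10 ppm, and the test is prespecified on a finalised database. Room for judgement is limited, though not absent.

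**Conclusion.** The point holds as a wrong statement in the article. Blinding of data entry and analysis is said to be achieved by means that conceal identity and add distance but do not conceal allocation. Many records expose the arm, and several planned analyses cannot be run without it.

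The consequence is a misdescribed safeguard. The trial and its primary comparison remain valid, and no numerical bias can be derived from the documents. The conclusion assumes that practitioner-visit and scan data sit in the files used for entry and analysis, as their role in the planned outcomes and adherence assessment implies. It does not assume that any outcome will be misclassified.

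**What to change.** Revise the Blinding section and the data flow in four steps.

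1. Withdraw the claim that data entry is blinded.
2. Fix in writing the rule that derives the primary outcome as now defined (quit date, continuous abstinence to the end of pregnancy, validation by carbon monoxide or cotinine), and lock each woman's status before the allocation code is linked. The endpoint must not change, and the quit-date and cotinine data must stay in the derivation. Whoever applies the rule may still guess the arm from some records, so the protection at this step comes from the fixed rule and the lock.
3. Give the remote statistician a primary-analysis file that holds only the locked outcome, the stratification factors and a neutral two-level arm code. Release the three-group code and the practitioner and scan fields after the primary result is recorded.
4. Limit the blinding claim to the primary analysis, and report the adherence, per-protocol, control-group and growth-restriction analyses as unblinded.

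The cost is one extra data export, a written derivation rule, a paragraph of text and a weaker blinding claim. The analysis is already remote from the centre, so no new staff should be needed.

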### Intervention

#### Study protocol

Patients in the STOP clinic have their booking visit between 10 and 19 weeks and see the obstetric team, midwife, and smoking cessation practitioner. Baseline demographics, educational level attained, health literacy, previous quit attempts, and motivation are assessed with a behavioural questionnaire. Data on the patient’s current smoking status and habits, including the use of other tobacco products and e-cigarettes, will be recorded and a measure of her level of addiction will be performed via the Fagerström test [12].

#### Clinic structure

At each visit the patient has her blood pressure measured and a dipstick urinalysis. Symphysio-fundal height (SFH) is recorded, liquor volume is assessed clinically, and the fetal heartbeat is checked. In cases of morbid obesity where the SFH is inaccurate, a single fetal abdominal circumference can be obtained. Fetal biometry will only be performed if clinically indicated—for example, if there is suspected growth restriction, macrosomia, or need for biometry secondary to history or additional risk factors. Patients will remain in the STOP clinic regardless of smoking status, quit attempts, or failure to quit.

Follow up antenatal visits are held at 28, 32, 36, 38, and 39–40 weeks and at postdates (Fig. 2). The schedule of assessments and interventions is shown in Fig. 3.

**Fig. 2 Fig2:**
[figure not shown]
STOP trial clinic structure

**Fig. 3 Fig3:**
[figure not shown]
SPIRIT figure

#### Ultrasound

An ultrasound scan is performed at booking (early second trimester) and between 20 and 22 weeks for anomaly screening. Additional growth scans are carried out at 32 and 36 weeks to screen for fetal growth restriction. Triplicate measures of biparietal diameter, head circumference, abdominal circumference, and femur length are obtained, and an estimate of fetal weight is calculated using the Hadlock formula [13]. Fetal adiposity is measured at the fetal thigh and abdomen as described previously [14]. Doppler measurements are obtained from both the umbilical and middle cerebral arteries. At the time of these growth scans, the self-reported number of cigarettes is recorded along with the timing of the last cigarette use. Exhaled carbon monoxide (CO) and urinary cotinine are measured. Images taken by the ultrasonographer are qualitatively controlled and scored according to the scheme described by Salomon et al. [15].

#### Smoking cessation program structure

A smoking cessation practitioner assesses the patient as part of the primary care giving team and measures exhaled CO. The Health Service Executive (HSE) Tobacco Cessation Support Program is a structured behavioural support program used by smoking cessation specialists in Ireland. It uses behavioural change techniques to support the tobacco user through the process of quitting by increasing confidence and motivation to quit and developing personal coping skills to sustain the quit attempt over time. Once the smoking cessation intervention is performed, a ‘quit date’ is set. The smoking cessation practitioner then sees the patient according to the following schedule:
One week post quit dateFour weeks post quit dateThree months post quit dateSix months post quit date/end of pregnancy (depending on gestation).

If a patient is still smoking at 4 weeks post quit date, NRT is offered in accordance with HSE guidelines which recommend its use in pregnancy only after a psychological intervention has failed.

The smoking cessation practitioner return visits are held in the clinic alongside the antenatal team. Current smoking status is recorded at each visit to the smoking cessation practitioner. If the patient has quit smoking, the timing of cessation and any aids used are recorded. Measures of urge to smoke, tobacco withdrawal score, and confidence in quitting are recorded. Quantitative measurement of urine cotinine is performed at 32 and 36 weeks, coinciding with the third trimester ultrasound scans. The HSE-adapted Russell Standard definitions of Quit are used [16]:
*Self-reported Quit*. This is defined as a self-report of smoking not more than five cigarettes from the quit date. A standard abstinence question is ‘Have you smoked at all since (date of start of abstinence period) A: No, not a puff; B: 1–5 cigarettes; C: More than 5 cigarettes?’ Answer A or B can be classified as a Self-reported Quit.*Validated Quit*. A Self-reported Quit that is validated with a CO monitor reading of less than 10 ppm is classified as a Validated Quit.

### Midwifery

The STOP clinic delivers both obstetric and midwifery expertise. The midwife in the STOP clinic provides support during the pregnancy, information on labor and delivery, and breastfeeding information. The midwife also coordinates referrals to antenatal classes and liaises with the multidisciplinary team when required.

### Postnatal assessment and qualitative measures

After delivery, a member of the research team meets the patient to perform a CO test. A pseudonymised questionnaire is provided to record her current smoking habits, information on cessation (if it has occurred), and any aids used. Satisfaction with care, confidence in healthcare providers, and confidence as an active participant in healthcare decisions are recorded with Likert-type scales. An Edinburgh Postnatal Depression Scale score is also recorded.

A final cessation check is performed at 6 months postnatal to screen for recidivism and is validated by a CO measurement, in line with the Russell Standard for reporting in smoking cessation clinical trials [16].

### Controls

The control group is 226 patients booked and recruited at the same time and randomised to ‘routine care.’ These patients have smoking cessation advice given as a ‘once-off’ at the booking visit via verbal or written information on the HSE Quit service, which is the current routine care in the Coombe and all obstetric units in Ireland [17]. The patients will attend either a general obstetric clinic or midwifery-led clinic and have a booking scan and 20–22-week anomaly scan as normal. The control group will be divided into two groups: 113 will have an additional scan at 32 and 36 weeks to screen for intrauterine growth restriction (IUGR), and 113 will receive no additional scans unless clinically indicated by their team. This is done to ensure testing of the hypothesis that the clinic as the intervention is responsible for any difference in outcomes, rather than the provision of additional ultrasound scans.

### Data management

Data collected in the study will be irrevocably anonymised, with patient names, hospital numbers, and routine testing specimen numbers de-identified and replaced with study numbers for the purpose of this research. The collected data will be stored in a password-protected spreadsheet on an encrypted computer and will be exported as a dataset for statistical analysis.

### Data and safety monitoring

The STOP trial reports to a Data and Safety Monitoring Committee composed of two independent clinicians with no involvement in the study, an independent statistician and an independent psychologist.

## Analyses

### Statistical analysis

Outcomes in the smoking cessation intervention group will be compared to those for all control patients in an intention-to-treat analysis. A 5% level of significance will be used in a chi-square test for a difference in overall smoking cessation rates. Post hoc testing will consist of comparing the two control groups, i.e. controls under routine care versus controls with third trimester study scans (screening for IUGR). In a secondary analysis, IUGR rates will be compared between the smoking cessation group and the control group screened for IUGR. An analysis of covariance (ANCOVA) analysis will be used to adjust for the stratification factors (age, parity, and history of fetal growth restriction). Intervention adherence will be assessed, and the group comparisons will be reproduced in a per-protocol population. Potential patient selection bias will be assessed using the Berger-Exner test. Statistical analysis will be performed using the STATA IC15 statistical package.

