### Primary outcome

The Russell Standard for reporting of smoking cessation in clinical trials will be followed [16].

The primary outcome is self-reported, continuous abstinence from smoking between the quit date and end of pregnancy, validated by exhaled CO or urinary cotinine. The quit date is targeted as being at or before 16 weeks’ gestation and no further than 28 weeks’ gestation.

Secondary outcomes are (see Additional file 1):
*Smoking*. Number of cigarettes smoked. Smoking cessation at 3 months post quit date, 6 months post quit date and/or end of pregnancy. Smoking cessation at 6 months postpartum*Psychological*. Urge to smoke, tobacco withdrawal symptoms, self-confidence in stopping smoking, self-reported depression at end of pregnancy*Fetal morbidity and mortality including neonatal measures*. Miscarriage, stillbirth, neonatal death, birth weight, estimated fetal weight at 32 weeks, estimated fetal weight at 36 weeks, spontaneous pre-term birth, iatrogenic pre-term birth, birth injury, neonatal complication, oxygen dependence, admission to neonatal unit, length of stay of neonate. Modified from Core Outcome Measures in Effectiveness Trials (COMET) Initiative [18]*Maternal morbidity and mortality including delivery outcomes*. Maternal death, mode of delivery, need for induction/delivery, maternal need for intensive care, maternal length of stay, pre-eclampsia, pregnancy-induced hypertension, postpartum haemorrhage, blood transfusion, late maternal complication. Modified from COMET Initiative [18]*Qualitative measures*. Satisfaction with the results of care, confidence as an active participant in healthcare decisions, confidence in healthcare providers.

The secondary outcomes are defined in detail in Additional file 1.

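### Estimated fetal weight at 32 and 36 weeks falls under the all-controls comparison, although half the controls have no scheduled scan then; the comparison is open to selection, probably but not certainly towards STOP

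*Protocol article*

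**What the plan says.** The Statistical analysis section of the protocol article sets one general comparator, by intention to treat: "Outcomes in the smoking cessation intervention group will be compared to those for all control patients". It names one departure from it: "IUGR rates will be compared between the smoking cessation group and the control group screened for IUGR".

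The list of secondary outcomes (under Primary outcome) includes "estimated fetal weight at 32 weeks, estimated fetal weight at 36 weeks". No separate comparator is given for these two.

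The arms differ in how these values come about. For STOP, the Ultrasound section says "Additional growth scans are carried out at 32 and 36 weeks to screen for fetal growth restriction". The Controls section says "The control group is 226 patients booked and recruited at the same time" and splits them. Of these, "113 will have an additional scan at 32 and 36 weeks to screen for intrauterine growth restriction (IUGR"), while "113 will receive no additional scans unless clinically indicated by their team". The same section explains that the split is meant to show whether the clinic, and not the extra scanning, accounts for any difference.

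**The concern.** EFW exists only where a scan was done. In STOP and in half the controls the scan is due by schedule; in the other half it depends on a clinician seeing a reason for it. Followed as written, the all-controls rule pools a scheduled sample with a sample picked by indication, and compares the mixture with a fully scheduled arm.

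The other parts of the analysis do not repair this. Intention to treat cannot supply an EFW that was never measured. Adjusting for age, parity and history of growth restriction does not account for suspicion that arises in the current pregnancy.

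At stake is a false signal on fetal growth. If indicated scans are mostly for small fetuses, pooled controls would look lighter than STOP even if the clinic did nothing. The trial's hypothesis is that more cessation leads to higher birth weight, so such a difference would be easy to read as support. The plan already avoids this for IUGR rates, which come from the same scans, but does not carry the restriction over to EFW.

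**Working it through.** **Inputs from the article.** 225 per arm (Sample size justification); 226 controls, 113 with scheduled scans and 113 without (Controls), so 113/226 = 50%; significance level 5%, taken as two-sided. The article gives no figure for EFW to reproduce. Its 225 per arm for 9% v 18% at 80% power is reproduced (226 by the two-sided pooled formula without continuity correction) and is used here only as the arm size.

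**Inputs assumed, because the article has none.** EFW is standard normal in SD units. A control without scheduled scans is scanned with probability a if her fetus is below -1 SD, and b otherwise, with a from 0.4 to 0.6 and b from 0.1 to 0.2. The clinic has no effect.

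**Formulas.** With P(Z < -1) = 0.1587 and normal density 0.2420 at 1:

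- share of the 113 with a value: f = 0.1587a + 0.8413b
- mean deficit of those values: d = 0.2420(a - b)/f
- downward shift of the pooled control mean: f·d/(1 + f)
- standard error (unit SD throughout, an approximation): sqrt(1/225 + 1/(113 + 113f))
- false-positive rate: two-sided 5% normal test with mean equal to the shift

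**Results at the corners of the assumed ranges.**

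| a | b | f | d (SD) | shift (SD) | SE (SD) | false-positive rate |
|---|---|---|---|---|---|---|
| 0.4 | 0.1 | 14.8% | 0.49 | 0.063 | 0.110 | about 9% |
| 0.4 | 0.2 | 23.2% | 0.21 | 0.039 | 0.108 | 6.5% |
| 0.6 | 0.1 | 17.9% | 0.67 | 0.103 | 0.109 | 15.5% |
| 0.6 | 0.2 | 26.3% | 0.37 | 0.077 | 0.107 | about 11% |

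Worked example, third row: f = 0.1587 × 0.6 + 0.8413 × 0.1 = 0.179; d = 0.2420 × 0.5/0.179 = 0.67; shift = 0.2420 × 0.5/1.179 = 0.103.

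**If large fetuses are scanned too.** Let c be the scan probability above +1 SD, so that the shift becomes 0.2420(a - c)/(1 + f), with f = 0.1587(a + c) + 0.6827b.

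- a = 0.5, b = 0.1: the shift is 0.083 when c = b, 0.040 when c = 0.3, and 0 when c = 0.5.
- a = 0.4, b = 0.2: the shift is 0.039 when c = b and 0.019 when c = 0.3.
- If c exceeds a, the sign reverses and the bias goes against STOP.

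**After restriction to scanned controls.** The selection term is zero. SE = sqrt(1/225 + 1/113) = 0.115 SD, and the detectable difference at 80% power is (1.96 + 0.84) × 0.115 = 0.32 SD. A full 225 v 226 comparison would give 0.26 SD, but it needs an EFW from every control, which the design does not collect.

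**The case against.** The strongest reply is that the bias needs indicated scans to be entered as the 32- and 36-week outcome. The outcome is named by the two scheduled time points, and the analysis section calls the extra control scans study scans. If only those feed EFW, the controls with a value are the scanned 113 and there is no bias. This stands as a possibility. The article does not say it, however, and the file that defines the secondary outcomes is not shown. That leaves the general comparator rule, which points to all controls.

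The second reply concerns direction. A reader might infer that the comparison simply favours STOP. The article does not establish that. Its examples of a clinical indication (Clinic structure, given for the STOP clinic) include macrosomia, history and other risk factors as well as suspected growth restriction. Towards STOP is the likelier direction, because the Background reports lower birth weight and more growth restriction in smokers, and the Conclusions say that women who need drug treatment for gestational diabetes are transferred out. But no mix is given.

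Two further readings are tempting and should not be drawn:

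- *That the bias matches the plausible true effect.* This would need an SD in grams and a weight gain per quitter, and the article gives neither. Every shift in the table is below one standard error.
- *That induction, iatrogenic pre-term birth and mode of delivery are wrongly pooled.* They can be recorded in every woman, so scanning does not select who has a value. Screening is part of the intervention (Abstract), and a comparison of the two control groups is already planned. A further STOP v scanned-controls comparison would be a preference, not a correction.

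The primary outcome and birth weight are unaffected.

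**Conclusion.** The point holds in limited form. As worded, the plan compares EFW at 32 and 36 weeks with a control arm of which half is measured only on indication. That admits selection bias if indicated scans are used, probably but not certainly in favour of STOP.

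If only low weight triggers extra scans, the shift is about 0.04 to 0.10 SD and the false-positive rate about 6.5 to 15.5% instead of 5%. These figures rest on assumed scan probabilities, a threshold at -1 SD, full arms and a common SD. With large fetuses also scanned the bias is smaller or absent, and with study scans only it is nil. It concerns one secondary outcome at two time points. It should be corrected because the repair costs almost nothing and follows the plan's own rule for IUGR rates.

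**What to change.** Add one sentence to the Statistical analysis section: EFW at 32 and 36 weeks is compared between STOP and the control group with scheduled third-trimester scans only, using values from those scheduled study scans in both groups. Keep birth weight and the delivery outcomes in the all-controls comparison.

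In the same edit, reconcile the Clinic structure section, which limits fetal biometry in the STOP clinic to clinical indication, with the Ultrasound section, which schedules growth scans at 32 and 36 weeks. The comparison depends on the STOP scans being scheduled.

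The cost is the loss of a few control values that were not observed at random, and a detectable difference of about 0.32 SD before dropout.
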